## Abstract

**Background:**

Chronic fatigue syndrome (CFS) is characterized by profound and disabling fatigue with no known somatic explanation. Cognitive behavioral therapy (CBT) has proven to be a successful intervention leading to a reduction in fatigue and disability. Based on previous neuroimaging findings, it has been suggested that central neural mechanisms may underlie CFS symptoms and play a role in the change brought on by CBT. In this randomized controlled trial we aim to further investigate the neural mechanisms that underlie fatigue in CFS and their change by CBT.

**Methods/Design:**

We will conduct a randomized controlled trial in which we collect anatomical and functional magnetic resonance imaging (MRI) measures from female CFS patients before and after CBT (N = 60) or waiting list (N = 30) and compare these with measures from age and education matched healthy controls (N = 30). By including a large treatment group we will also be able to compare patients that benefit from CBT with those that do not. In addition, to further investigate the role of endocrine and immune biomarkers in CFS, we will determine cortisol and cytokine concentrations in blood, hair and/or saliva.

**Discussion:**

This project creates an unique opportunity to enhance our understanding of CFS symptoms and its change by CBT in terms of neuroanatomical, neurofunctional, endocrinological and immunological mechanisms and can help to further improve future treatments strategies.

**Trial registration:**

Dutch Trial Register #15852. Registered 9 December 2013 (http://www.trialregister.nl/trialreg/admin/rctview.asp?TC=4311)

## Background

Chronic fatigue syndrome (CFS) is characterized by severe fatigue persisting at least 6 months and leading to considerable impairment in daily functioning ([1]; Reeves et al., [2]). Various accompanying symptoms may be present, such as joint and muscle pain, headaches, impaired memory and concentration, and exercise intolerance. The aetiology of CFS is currently unknown; symptoms are not explained by a known medical condition and are not alleviated by rest (Prins et al., [3]). Cognitive behavioral therapy (CBT) for CFS, a treatment that aims to change behavior and cognitions thought to perpetuate symptoms, has shown to be an effective treatment for CFS patients [4]. Following treatment, the majority of CFS patients show improvement in symptoms and a subgroup even fully recovers from CFS (Knoop et al., [5]; White et al., [6]).

Little is known about the mechanism of change of CBT for CFS. Thus far, mediation analysis of randomized controlled trials testing the efficacy of CBT suggested that the reduction of fatigue and disability is mediated by a change in cognitions, such as decreased focusing on symptoms and changes in illness beliefs ([7]; Knoop et al., [8]; Wiborg et al., [9]; Wiborg et al., [10]), rather than changes in physical fitness ([7]; Wiborg et al., [11]). These findings implicate that neural mechanisms underlying these cognitions may play an important role in CFS. This suggestion is further supported by accumulating evidence from neuroimaging studies demonstrating neural abnormalities in CFS patients [12]. Thus, several neuro imaging studies have found reduced grey matter volumes ([13, 14]; Okada et al., [15]), white matter changes (Zeineh et al., [16]). and functional abnormalities in prefrontal, parietal, and limbic regions for CFS patients versus healthy controls ([17–20]; Lange et al., [21]). In addition, a recent positron emision tomography (PET) study demonstrated increases in microglia activity, suggestive for neuroinflammation (Nakatomi et al., [22]). Moreover, one neuroimaging study also demonstrated that treatment of CFS with CBT increased grey matter volume in CFS patients. These changes were located in the dorsolateral prefrontal cortex (DLPFC) [14], a region associated with cognitive-regulatory functions. Similarly, CBT-related anatomical and functional changes have been reported in other conditions such as chronic pain (Seminowicz et al., [23]) and mood and anxiety disorders (Beauregard, [24, 25]; Strauman et al., [23]). Accordingly, we suggest that a reduction in fatigue and disability brought on by CBT for CFS is accompanied and possibly mediated by anatomical and functional changes in the brain.

So far, definitive evidence for this argument is limited because the few existing studies have often used small samples sizes and lacked a patient control group. The inclusion of a patient control condition is necessary to attribute changes seen in the treatment group to the intervention, rather than to time per se or to changes occurring irrespective of the treatment. In this study we will address these issues and aim to further investigate neural mechanisms underlying CFS and its change by CBT using anatomical and functional magnetic resonance imaging (MRI) in a large-sample randomized controlled trial (RCT). In this RCT, we will compare changes between CFS patients that had CBT (N = 60) with patients that were allocated to a waiting period (N = 30). By including the large treatment group we will also be able to investigate the relationship between neural changes and treatment response. Patients will be compared with healthy controls (N = 30) who are also tested twice, separated by 6 months, to control for test-retest effects.

This study will investigate neural mechanisms underlying CFS symptoms and its changes after CBT. The aims are threefold. First, we aim to replicate previous found anatomical CBT-related changes in grey matter volumes [14] using anatomical MRI and qualify these findings by exploring changes in metabolite concentrations and white matter integrity using magnetic resonance spectroscopy (MRS) and diffusion tensor imaging (DTI). Second, we aim to explore the mechanisms of change of CBT for CFS using functional MRI (fMRI) and behavioral testing. Finally, we aim to investigate immune and endocrine functioning in CFS and its change after CBT by assessing various biomarkers in blood, saliva and hair. These three aims are discussed in more detail below.

### Anatomical changes in CFS

Our first aim is to replicate and extend previous found anatomical changes in grey matter volumes [14] by including a larger treatment group and a patient control group. Furthermore, we aim to provide additional information about the nature of anatomical changes by exploring changes in metabolite concentrations using magnetic resonance spectroscopy (MRS) and white matter integrity using diffusion tensor imaging (DTI).

MRS allows for the identification and quantification of various metabolites in the brain like N-acetylaspartate (NAA), myo-inositol, choline, creatine glutamate/glutamine. These metabolite concentrations can inform us about the nature of grey matter changes. For example, while NAA is mainly present in the neurons and provides a marker of neuronal health (Moffett et al., [26]), myo-inositol is mainly associated with glia-activation and provides a marker of neuroinflammation [27]. Previous work in small samples of CFS patients (N < 11) has reported reduced NAA levels in the hippocampus [28] as well as increased choline/creatine ratios in the occipital cortex (Puri et al., [29]), prefrontal cortex (Tomoda et al., [30]) and basal ganglia (Chaudhuri and Behan, [31]) , compared with healthy controls. Similarly, alterations in MRS measures have been reported in other medically unexplained conditions such as chronic pain (see review (Harris and Clauw, [32])) and irritable bowel syndrome (Niddam et al., [33]). MRS measures have shown to vary as a function of pain sensitivity ([34]; Petrou et al., [35]) or pain catastrophizing ([36]; Niddam et al., [33]). Moreover, some pilot studies show that NAA levels are subject to change following behavioral therapies [37] (O’Neill et al., [38]; Zurowski et al., [39]) suggesting that NAA reductions are reversible and can be used to monitor treatment response. In this project, we will investigate CBT-related metabolite changes in the DLPFC, as our aim is to assess the nature of previously reported grey matter changes in this region [14]. However, given that previous studies in CFS found metabolite differences in various brain regions, regional specificity to the DLPFC will be investigated by comparing changes in the DLPFC with those in the occipital cortex.

DTI is a technique that is sensitive to microstructural organization of neural tissues, measuring both the directionality and the magnitude of water diffusion (Beaulieu, [40]). To our knowledge, only one study has used DTI to investigate white matter in a small sample of CFS patients (N = 15) and report increased fractional anisotropy (FA) values in CFS patients compared with healthy controls in the right arcuate fasciculus, a white matter pathway that connects the frontal lobe with the inferior parietal lobe (Zeineh et al., [16]). In this project we will assess DTI measures in a larger sample and also explore possible changes after CBT.

### Functional changes in CFS

Our second aim is to explore the mechanisms of change of CBT for CFS by means of functional MRI and behavior. Task-dependent functional neuroimaging provides information about neural mechanisms that underlie specific processes involved in the execution of a specific task. Accordingly, task selection should always be done against the background of relevant cognitive and neural models of the disorder ([12]; Strauman et al., [23]). For this project, task-selection was based on a combination of a neurobiologically informed Bayesian model of somatoform symptoms [41] and clinical observations. The recently developed Bayesian model describes somatoform symptoms in terms of altered perception resulting from an inference failure between sensory information and prior beliefs [41]. In the light of CFS, the model suggests that increased perception of symptoms may arise from pathologically precise prior beliefs that affect sensory perceptions and attributions. This model exploits some key factors that have been identified by clinical cognitive behavioral models of CFS and that are challenged by CBT for CFS including the role of fatigue related beliefs (e.g. about the ability to engage in physical activities) and the attention towards symptoms ([7]; Knoop et al., [8]; Vercoulen et al., [42]; Wiborg et al., [9]). In addition, clinical observations demonstrate that symptoms often involve physical activities. Thus, CFS patients show reduced activity levels (Nijs et al., [43]; Werf et al., [44]) and underperformance on physical exercise tasks (Fry and Martin, [45]; Riley et al., [46]; Schillings et al., [47]). These decreases in physical activities are suggested to result from reduced expectations about physical abilities (Heins et al., [48]; Nijs et al., [49]), fear avoidance beliefs (e.g. the fear that exercise will make symptoms worse) and avoidance behaviors, which are highly prevalent in the CFS population ([50]; Nijs et al., [51]). Indeed, a recent clinical trial revealed that changes in fear avoidance beliefs and avoidance behavior mediate the CBT effects in CFS patients [7]. Following the neurobiological informed model and these clinical observations, we aim to investigate neural mechanisms underlying inference processes during effortful physical exertions using two fMRI paradigms. In addition, we will also explore general inference processing in the visual domain using a behavioral paradigm.

In the first fMRI paradigm we will investigate effort perception during an effort task, using a MR-compatible handgrip device. Neural activity will be assessed during preparation of low, medium and high effort production and in response to task-feedback indicating that the subjects provided too much, too little or the correct amount of effort. Previous work has already demonstrated that CFS patients show alterations in neural error processing during a motor imagery task [20]. This study will extend these findings by testing whether alterations in motor preparation and error processing are consistent with the known fatigue-related beliefs. To this end, we will test the hypothesis that CFS patients show alterations in neural feedback-processing towards errors that indicate that too little versus too much physical effort has been produced and that these alterations vary as a function of effort level. We hypothesize that successful CBT outcome is accompanied by normalization of these alterations.

In the second fMRI task we aim to investigate alterations in neural processes underlying effort avoidance learning. CFS has been associated with increased avoidance of physical activities (see above). However, it is unclear whether these avoidance behaviors are due to the increased experienced effort of physical activities or whether CFS patients develop dysfunctional beliefs about the need to avoid physical activities. We will assess neural mechanisms underlying the inferring of contingencies between cues and effortful handgrip-contractions, using an adapted version of the salience attribution task (Roiser et al., [52]; Roiser et al., [53]). This task allows for dissociating avoidance learning that is adaptive, i.e. developing avoidance only for cues that are predictive for effortful outcomes, from avoidance learning that is non-adaptive, i.e. developing dysfunctional avoidance, also for cues that are not predictive for effortful outcomes. We will test two hypotheses: 1) CFS patients will show increased adaptive avoidance learning compared to healthy controls, which is suggestive of an increased impact of the experienced effort on avoidance learning. 2) CFS patients will show increased non-adaptive avoidance learning, which is suggestive of a higher tendency to develop dysfunctional expectations for cues that are not predictive for effortful outcomes. We hypothesize that successful CBT is accompanied by normalization of (non-) adaptive avoidance learning.

In the behavioral task we aim to investigate general inference processes in CFS patients. The Bayesian model suggests that the perception of medically unexplained symptoms result from prior beliefs that are afforded too much precision. Thus, an increased general tendency to base perceptual decisions more on prior information than on sensory inputs in any sensory domain may reflect a fundamental vulnerability that may predispose subjects to develop CFS. Here we aim to test this hypothesis in the visual domain by investigating the influence of informative cues on decisions about the direction of moving dots using the well developed moving dot paradigm (Rahnev et al., [54]).

### Immune and endocrine changes in CFS

Finally, we aim to investigate immune and endocrine changes in CFS. Cytokines are small proteins that play a key role in normal physiology and disease. Because of the resemblance of CFS symptoms with so called “sickness behavior” including the symptoms fatigue, post-exertional malaise and reduced activity levels, CFS has often been suggested to involve increased activity of pro-inflammatory cytokines, such as IL-1β and TNF-α which are considered to play a key role in inducing sickness behavior during acute illness ([55]; Kelley et al., [56]). In this project we will not only assess cytokine concentrations in blood plasma, but also evaluate cytokine activity at the mRNA level using pax-gene tubes. Previous studies on this subject have met with inconsistent results (Lyall et al., [57]). One explanation is that cytokines in the body respond to a variety of external and environmental stimuli like stress and exercise. To control for such influences, we will select well-matched controls that will follow exactly the same procedures during each test day. In addition, cytokines will not only be measured in blood plasma, but also at the mRNA level using pax-gene tubes.

Disturbances in hypothalamic-pituitary-adrenal (HPA)-axis functioning have been associated with fatigue and CFS symptoms (Powell et al., [58]; Silverman et al., [59]; Tak et al., [60]). More specifically, previous work shows that CFS patients are characterized by hypo-cortisolism (Nater et al., [61]a; Nater et al., [62]b), which can normalize to levels comparable to healthy population after CBT in adolescents (Nijhof et al., [63]; Rimes et al., [64]) and adults (Roberts et al., [65]). In this project we will replicate and extend these findings, by assessing both diurnal cortisol fluctuations in saliva as well as baseline cortisol levels of the past month in hair.

### Summary

This project aims at investigating neural mechanisms underlying CFS symptoms and its changes after CBT by collection anatomical MRI measures, functional MRI measures, behavioral measures and blood, saliva and hair sampling. We will extend previous neuroimaging work by collecting data form a large group of subjects and by including a patient control condition in a RCT. This project creates a unique opportunity to enhance our understanding of CFS symptoms and its change by CBT in terms of neuroanatomical, neurofunctional, behavioural, immunological and endocrinological mechanisms.

## Methods/design

### Study design

A RCT will be conducted to investigate neural correlates of change brought on by CBT in patients diagnosed with CFS. CFS patients will be randomly assigned to either the intervention group (N = 60), which will immediately start with CBT, or the waiting group (N = 30), which will start with CBT after a 6 months waiting period. In order to compare CFS patients that recover from CBT with those that do not we will use a 2:1 allocation ratio for CBT and waiting group respectively. MRI measurements, behavioral measures, questionnaires and biomarker sampling will be gathered at baseline and at a second session after approximately 6 months in both groups. Results will be compared to 30 age, gender and education matched healthy controls, which will also be tested twice, separated by a 6 months period (Fig. 1).

**Fig. 1 Fig1:**
[figure not shown]
Trial design. CBT = Cognitive behavioural therapy

### Ethical aspects

The study is approved by the Medical research ethics committee and Central Committee on Research Involving Human Subjects (registration number NL43606.091.13). This study will be conducted according to the principles of the declaration of Helsinki. CFS patients will be recruited from the Expert Centre for Chronic Fatigue (ECCF). Participants will be informed about the study and written informed consents will be obtained before the first testing day and randomization.

Participants can withdraw from the study at any time, and for any reason, without consequences. The investigator can decide to withdraw a participant from the study in case of late disclosure of exclusion criteria (e.g. psychiatric co-morbidity) or a change in meeting in- and exclusion criteria (e.g. when participant decides to start psychotropic medication after inclusion). CFS patients who (are) withdraw(n) from the study will continue to receive treatment at the ECCF. Patients that withdraw before randomization or did not start face-to-face CBT when assigned to the CBT condition and participants that are withdrawn by the investigator will be replaced when time allows. Patients that received CBT for CFS outside the ECCF during their waiting list period will be excluded from analysis.

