### Study population and recruitment procedure

A total of 90 female CFS patients and 30 age and education matched female healthy controls will be recruited from the ECCF of the radboudUMC in Nijmegen, the Netherlands. Only female patients are included for homogeneity. Patients that are referred to the ECCF of the Radboudumc, are diagnosed with CFS according to the US Centers for Disease Control and prevention (CDC) consensus-criteria ([66]; Reeves et al., [2]), and scoring 40 or higher on the subscale fatigue severity of the Checklist Individual Strength (CIS) and have a total score of 700 or higher on the Sickness Impact Profile 8 (SIP8) will be informed about the study by their treating psychologist during their first intake session at the ECCF. If the patients agree, they will receive an information folder. The investigator will call the patients after a one week reflection period to answer any further questions and to ask for participation. If willing to participate, and meeting all in- and exclusion criteria (Table 1), patients will be invited for the first testing day at the Donders institute for brain cognition and behavior. Age and education matched female healthy controls will be recruited though advertisements and through flyers in the patients folder. Interested healthy controls will receive an information folder and the recruitment procedure will follow the same steps as described above. Written informed consent will be given at the first session day. Randomization of patients will take place after the first session day. The Mini-international Neuropsychiatric Interview (M.I.N.I) will be used to rule out any current psychiatric disorders.

**Table 1 Tab1:** Inclusion and exclusion criteria

Inclusion criteria	
1.	Female
2.	Age between 18 and 55 years
Additional inclusion criteria for CFS patients	
1.	CFS diagnosis according to the CDC-criteria ([66]; Reeves et al., [2]);
2.	Fatigue severity subscale (CIS) score ≥40
3.	Severely disabled, defined by scoring ≥ 700 on the Sickness Impact Profile (SIP)
4.	Eligible for treatment with CBT
Additional inclusion criteria for healthy controls	
5.	Fatigue severity subscale (CIS) score ≤ 35
Exclusion criteria	
1.	Current use of psychotropic medication (e.g. antidepressants)
2.	Contra-indication for MR-examinations (e.g. claustrophobia)
3.	Abnormal hearing or (uncorrected) vision

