### Analysis

The aim of this project is to explore the neural mechanisms of change underlying (successful) CBT for CFS. Accordingly, we will include all patients that completed both sessions for analysis of CBT effects. Statistical analysis will be done to 1) compare outcome measures between CFS patients and healthy controls at baseline, 2) compare changes between baseline and second assessment between patients that had CBT and waiting list and 3) compare changes between baseline and second assessment between CFS patients within the CBT condition that show clinical significant improvement (see above) and those that do not. Following previous reports [13, 14], relationship between neural outcome measures and clinical outcome measures, physical activity levels and neuropsychological functioning will be assessed. Multiple mediation analyses will be conducted to explore whether neural outcome measures mediate therapy effects on clinical outcome measures (Preacher and Hayes, [91]).

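### No as-randomised analysis of CIS fatigue and SIP8 is described, and waiting-list patients who obtained CBT elsewhere are excluded after allocation, which probably enlarges the CBT effect

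*Protocol article*

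**What the plan says.** Under Study population and recruitment procedure: "Randomization of patients will take place after the first session day". Every rule below that concerns treatment received or a later change therefore acts after allocation.

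Ethical aspects gives three such rules.

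- Waiting list: "Patients that received CBT for CFS outside the ECCF during their waiting list period will be excluded from analysis".
- CBT arm: replacement covers patients who "did not start face-to-face CBT when assigned to the CBT condition and participants that are withdrawn by the investigator will be replaced", time permitting. The sentence is about replacement. It does not say whether the non-starter leaves the analysis.
- Either arm: the investigator may withdraw a participant for "a change in meeting in- and exclusion criteria", with starting psychotropic medication after inclusion as the example. The Randomization section adds that the researchers who collect and analyse the data know the allocation.

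The Analysis section fixes the analysis set: "we will include all patients that completed both sessions for analysis of CBT effects". The randomised contrast is to "compare changes between baseline and second assessment between patients that had CBT and waiting list". No analysis of all randomised patients in their allocated arms is described.

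Outcome measures names CIS fatigue and SIP8 as the primary clinical outcomes. The Background says that a patient control condition is needed so that change can be attributed to the intervention. The Sample size section claims enough power for treatment effects on the primary clinical outcomes.

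**The concern.** CBT against waiting list is the only randomised contrast in the study. It supports attribution to CBT only while the groups compared are the groups that were randomised. The outside-CBT exclusion applies to one arm and depends on what patients do after allocation. If non-starters are also left out of the CBT arm, a second selection works alongside it: one rule removes treated patients from the control arm, the other removes untreated patients from the treatment arm. Discretionary withdrawal for later events, by staff who may know the allocation, adds a further route for selection.

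At stake are the CBT effect on CIS fatigue and SIP8 and the therapy effect that the planned mediation analyses seek to explain. A scan pair cannot exist without two sessions, so a completer set is natural for imaging. The clinical outcomes are different: Session procedure says that patients' questionnaires come from the clinic's routine, and the Sample size section says that scan failure does not affect clinical measures.

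**Working it through.** **1. Which rules differ by arm**

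| Rule | CBT arm | Waiting list |
|---|---|---|
| Outside CBT | no rule | excluded from analysis |
| CBT not started | replaced; analysis status unstated | not applicable |
| Withdrawal by investigator | same wording | same wording |
| Both sessions required | same wording | same wording |

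Only the first row is an explicit arm-specific exclusion. The second becomes one if replaced means dropped.

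**2. The plan's own figure**

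Inputs from Sample size: change −15.2 (SD 15.8) with CBT and −5.2 (SD 7.2) on the waiting list, alpha 0.05 (two-sided assumed), power 0.95, ratio 2:1. That sentence names no scale; I read it as CIS fatigue.

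- Common SD = √[(15.8² + 7.2²)/2] = √150.74 = 12.28.
- Waiting-list n = (1 + 1/2) × (1.960 + 1.645)² × 150.74 / 10² ≈ 29.4, so 30, with 60 for CBT.
- Power at 60:30 is 0.954 (normal) or 0.950 (noncentral t).

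The stated size reproduces. The sample size is not at fault.

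**3. Effect of the exclusions if CBT works as assumed**

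Let f be the share of the CBT arm that never starts and g the share of the waiting list that obtains CBT elsewhere. The documents give neither. Assume that starters change by −15.2, non-starters change like waiting-list patients (−5.2), and outside-CBT patients change like CBT patients (−15.2).

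- CBT mean as randomised = −15.2(1 − f) − 5.2f
- Waiting-list mean as randomised = −5.2(1 − g) − 15.2g
- Difference = 10(1 − f − g)

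If both groups are dropped, the analysis estimates 10.0.

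| f | g | CBT mean | Waiting-list mean | As-randomised difference | Overstatement |
|---|---|---|---|---|---|
| 5% | 0 | −14.7 | −5.2 | 9.5 | 0.5 |
| 10% | 0 | −14.2 | −5.2 | 9.0 | 1.0 |
| 10% | 5% | −14.2 | −5.7 | 8.5 | 1.5 |
| 10% | 10% | −14.2 | −6.2 | 8.0 | 2.0 |
| 17% | 10% | −13.5 | −6.2 | 7.3 | 2.7 |

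If non-starters stay in, the planned analysis estimates 10(1 − f). The overstatement is then 10g alone: 0 to 1.0 point for g from 0 to 10%.

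**4. If CBT had no effect and non-starters were dropped**

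If non-starters fare δ points worse than starters, the spurious benefit is f × δ. For f of 5–17% and δ of 3–10 (both assumed), it runs from 0.05 × 3 = 0.15 to 0.17 × 10 = 1.7 points. At 50:25, which is 60:30 after 17% drop-out, the two-sided type I error is 0.05–0.10 with SDs of 15.8 and 7.2, and up to 0.16 with SD 7.2 in both arms.

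**5. Power of an as-randomised analysis**

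With all 60:30 followed up and the SDs unchanged, power for differences from 9.5 down to 7.3 is 0.97 to 0.85 allowing unequal variances, or 0.93 to 0.76 with the common SD of 12.28.

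**The case against.** The strongest reply is that this is a mechanistic study. The Analysis section says so and ties the completer set to that aim, and efficacy is presented as already established. For imaging this stands. It does not cover the clinical outcomes, for which the article claims power, or the Background's reliance on the control arm for attribution.

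Second, replacement is not exclusion. This also stands. A reader might infer that non-starters leave the analysis, or that their substitutes bypass randomisation. The text says neither: a non-starter who attends the second session meets the Analysis criterion, and allocation is per patient through a central web-based program. Recruiting extra patients through that program does not by itself bias the contrast. What remains is an ambiguity between Ethical aspects and Analysis that must be reconciled.

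Third, investigator withdrawal and the two-session requirement are worded alike for both arms, and late-disclosed exclusion criteria concern eligibility. It would therefore be wrong to say that all the rules differ by arm. The risk in withdrawal lies in discretion over events after allocation when the allocation is known. The two-session rule concerns assessments, so a patient who stops CBT but returns for the second session stays in.

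Fourth, a statistical analysis plan might hold an as-randomised analysis. That would excuse silence, but the article states the analysis set and the outside-CBT exclusion positively.

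Finally, continued clinic care does not guarantee usable questionnaires from someone who has left the study, which participants are free to do. That limits the remedy to those who still consent.

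**Conclusion.** The point holds in limited form. The outside-CBT exclusion is an explicit arm-specific exclusion after randomisation, the status of CBT non-starters is unresolved, and the only analysis set stated is completers of both sessions, for the clinical outcomes as well as for imaging. On the plan's own means, the as-randomised difference would be about 9.5 to 7.3 CIS points in place of 10.0. This assumes 5–17% non-starters who are dropped, 0–10% outside CBT, and the changes assigned to those groups in the working. None of these shares is in the documents.

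The direction is expected, not certain. If CBT had no effect, it would depend on the prognosis of those removed, and waiting-list patients who seek CBT elsewhere could be the worse cases.

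Three stronger inferences are not supported.

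- A reader might shrink the expected CBT change, or the expected 50% success rate, by the 17% drop-out. The documents do not show that those expectations describe completers only, and the 17% is drop-out from the study, not failure to start CBT.
- A reader might take withdrawal for changed criteria to cover a patient whose CIS falls below the entry score of 40. Success is defined as a score below 35 with reliable change, so that reading would defeat the planned comparison of improved and unimproved patients.
- A reader might extend the point to the responder groups. Improvement is a per-patient criterion, and that comparison lies within the CBT arm and is not randomised.

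**What to change.** - State that the main CBT versus waiting-list analysis of CIS fatigue and SIP8 compares patients as randomised, using all available data.
- Remove the outside-CBT exclusion from that analysis.
- State that non-starters and patients withdrawn for changes after randomisation stay in their allocated arm in that analysis, even if extra patients are recruited, and that any extra patients enter through the same randomisation. This reconciles Ethical aspects with Analysis.
- Seek CIS and SIP8 at the second assessment from every randomised patient who still consents, whatever treatment was received.
- Keep the completer/treated set for paired imaging and, for the clinical outcomes, as a labelled secondary mechanistic analysis.

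The cost is a change of wording and modest follow-up effort, since the questionnaires are already part of clinic routine. The contrast is slightly diluted, with the loss of power shown in step 5 of the working.
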